## Abstract

**Background:**

The rapid ageing of the population is becoming an area of great concern, both globally and in Australia. On a societal level, the cost of supporting an ageing demographic, particularly with their associated medical requirements, is becoming an ever increasing burden that is only predicted to rise in the foreseeable future. The progressive decline in individuals’ cognitive ability as they age, particularly with respect to the ever increasing incidence of Alzheimer’s Disease (AD) and other cognitive complications, is in many respects one of the foundation stones of these concerns. There have been numerous observational studies reporting on the positive effects that aerobic exercise and the Mediterranean diet appear to have on improving cognitive ability. However, the ability of such interventions to improve cognitive ability, or even reduce the rate of cognitive ageing, has not been fully examined by substantial interventional studies within an ageing population.

**Methods:**

The LIILAC trial will investigate the potential for cognitive change in a cohort of cognitively healthy individuals, between the ages of 60 and 90 years, living in independent accommodation within Australian aged care facilities. This four-arm trial will investigate the cognitive changes which may occur as a result of the introduction of aerobic exercise and/or Mediterranean diet into individuals’ lifestyles, as well as the mechanisms by which these changes may be occurring. Participants will be tested at baseline and 6 months on a battery of computer based cognitive assessments, together with cardiovascular and blood biomarker assessments. The cardiovascular measures will assess changes in arterial stiffness and central pulse pressures, while the blood measures will examine changes in metabolic profiles, including brain derived neurotrophic factor (BDNF), inflammatory factors and insulin sensitivity.

**Conclusion:**

It is hypothesised that exercise and Mediterranean diet interventions, both individually and in combination, will result in improvements in cognitive performance compared with controls. Positive findings in this research will have potential implications for the management of aged care, particularly in respect to reducing the rate of cognitive decline and the associated impacts both on the individual and the broader community.

**Trial registration:**

Australia New Zealand Clinical Trial Registry-ACTRN12614001133628

## Background and rationale

The decline in cognitive ability with increasing age has been well established [1–4] and is associated with a reduction of functioning in areas such as attention regulation, processing speed and memory capacity [5]. This phenomenon of cognitive decline is of considerable concern on an individual level. In ageing and elderly populations significant concerns exist regarding the loss of mental faculties and independence of living, which is a cause of considerable psychological distress [1].

On a societal level this phenomenon is also of substantial concern, particularly with the current rapid ageing of the population. The over 60s are the fastest growing age demographic on Earth [6]. It is predicted, that almost one third of the total population of the planet will be aged 60 years or older by 2100 [7], with this percentage predicted to be reached by just 2025 in the Pacific/Oceanic region [8]. In Australia alone, the combined financial cost of formal and informal care of those with cognitive impairment and dementia was estimated to be around AU$8.2 billion in 2010 [9]. This cost is expected to rise to over AU$28 billion by 2040, causing considerable strain on the economy. It has also been predicted that a reduction of just two years in the onset of care requirements due to these age related cognitive issues could result in a 10 % reduction in the overall financial burden [9]. Given the societal and personal consequences, understanding the mechanisms behind the differential rates of cognitive ageing, and designing strategies to prevent or reduce the rate of cognitive decline that are simple and cost effective to implement, are of critical importance.

## What is cognitive ageing?

While there are multiple ways to characterise cognitive ability, it is commonly divided into crystallised intelligence and fluid intelligence. Crystallised intelligence refers to the knowledge and skills that are accumulated over a lifetime [10, 11]. This includes mental functions such as verbal ability, general knowledge and some numerical abilities [2]. Fluid intelligence, often highly associated with cognitive speed [12], refers to the ability to process information, think abstractly and solve problems. This includes aspects of memory, executive functioning and reasoning, and is considered to be largely innately determined [2, 13]. There is general consensus that while crystallised intelligence remains intact until late old age, fluid abilities decline progressively from middle adulthood onwards [14, 15]; and this decline appears to affect a number of fluid cognitive functions simultaneously. However, while the average performance on most fluid cognitive tasks have been found to decline with age, many studies have shown that some older people display comparatively little change, whereas others deteriorate quite rapidly [16, 17] and that this variability increases with increasing age [5].

Earlier research on the relationship between age and cognitive decline indicates that an individual’s cognitive performance increases up until adolescence or early adulthood and then progressively declines. However, the age at which decline begins and the extent of decline varies for different abilities [18]. It is the ageing brain and the consequences of long term effects on the brain that result in speed and memory performance decline [10, 14]. The ageing of the brain may be considered as a progressive and inevitable process potentially related to inflammation, the accumulation of oxidative stress and the related damage to cellular structures of the brain [19]. During normal ageing the brain may suffer morphological and functional deterioration that will potential affect neurotransmission and the alteration of motor and sensory systems, sleep, memory and potential learning [19–22].

A comprehensive review of earlier studies concluded that a slower rate of cognitive ageing could be predicted to a certain degree (along with other factors such as more years of education and an absence of the APOE ε4 allele) by an active lifestyle and better cardiovascular health [10]. This apparent effect of cardiovascular health on the rate of cognitive decline associated with increasing age has also been found by numerous recent studies [23–25]. More specifically, along with avoidance of smoking and limited alcohol consumption, optimisation of cardiovascular health can be most readily achieved through regular exercise and an anti-inflammatory diet focused on fruits and vegetables, such as the Mediterranean diet [26].

## Cognition and exercise

Numerous studies have identified benefits of exercise training for the cognitive functioning of older adults [27]. A meta-analysis, published in 2012, of 29 studies in older adults free from dementia, demonstrated that aerobic exercise interventions, ranging from 8 to 72 weeks, improved cognitive faculties including attention, processing speed, executive function, and memory [28] In a recent Australian study, older participants engaged in moderate aerobic exercise for 50 min three times per week for 6 months [29]. At the end of the study period, individuals in the exercise condition showed enhanced cognition in comparison to those not engaged in the exercise regime.

The cognitive benefits of exercise appear to increase with frequency of exercise [30], and are greatest for moderate (31–45 min) duration exercise sessions [27]. Whilst it has been suggested that the greatest cognitive improvements may occur when aerobic exercise is combined with strength training [28], there is evidence that walking programs may also be effective to improve cognitive function [31]. In a recent study conducted in seniors, half of the participants took part in a 90 min weekly walking program and half served as a control group [32]. After 3 months there was a significant improvement in word fluency, social interaction and motor function in those who participated in the walking program.

Several mechanisms of action have been proposed to account for the cognitive benefits of exercise in older adults. Long term effects of exercise may have indirect effects upon neurocognitive functioning by reducing diabetes, hypertension and cardiovascular disease [33]. Exercise may also have direct effects on brain physiology. There is increasing evidence that extended periods of exercise leads to increased volume of the hippocampus, a brain region vital for memory function, as well as reducing the rate of cerebral grey matter shrinkage [34]. Shorter term mechanisms have also been proposed, due to the identification of cognitive improvements following exercise interventions of several months [28]. For example, exercise may protect against inflammatory processes and regulate growth factor signalling in the brain [33]. Furthermore it has been suggested that exercise may interact with BDNF, a neurochemical which modulates brain plasticity, neuritic outgrowth, synaptic function, and can stimulate adult hippocampal neurogenesis [34].

## Cognition and diet

Dietary factors are considered to have a powerful influence on brain function on a daily basis [35]. With respect to the type of diet that may be of long term benefit, it has been found that people who adhere to a Mediterranean-style diet could reduce the potential for progression from healthy cognitive function to mild cognitive impairment (MCI) and subsequently to dementia [36–39]. Additionally, a diet higher in components of the Mediterranean diet has been found to correlate positively with reduced changes in Mini Mental State Examination (MMSE) scores over five or more years in cognitively healthy people over the age of 65 [40–42]. The Mediterranean diet refers to the dietary practices of populations from the Mediterranean regions. This diet consists predominantly of fruits, vegetables, nuts, cereals, legumes, fish and olive oil, with a moderate intake of alcohol and lower consumption of red meat and poultry. Adherence to the Mediterranean diet has also been linked to lower risk of mortality and vascular events [43], as well a reduction in the incidence of MCI [38].

It has also been found that specific nutritional intake has an impact on overall mental health and function [44]. Antioxidant-rich and flavonol containing components of the Mediterranean diet have been correlated with better performance on spatial working memory in younger women, aged 19 to 30 years, in as little as 10 days [45]. This correlation was also found across multiple measures of memory in people aged 55 to 80 years [46].

Similar to exercise interventions, it is likely that vascular processes and inflammatory pathways may also mediate the relationship between the Mediterranean diet and cognition. An eight week Mediterranean diet intervention has been showed to reduce circulatory markers of inflammation [47, 48]. This may be due to the combined effects of a range of components of the Mediterranean diet. A higher intake of fruit and vegetables has been associated with higher blood nutrient levels, lower oxidative stress and better cognitive function [49]. A high consumption of fruit and vegetables, or a diet that is full of antioxidants, carotenoids, vitamins, fibre and magnesium, has been shown to be beneficial in reducing C-reactive protein (CRP) levels, a marker of inflammation closely linked to cognition [50]. In addition, flavonoids found in fruit and vegetables, and omega-3 polyunsaturated fatty acids found in high quantities in fish, have demonstrated anti-inflammatory, cardio-protective and neuro-protective properties [51, 52].

The cardio-protective nature of the Mediterranean diet has been investigated through an intervention study involving 342 participants. This study found that on a 10 point Mediterranean diet adherence scale, even a 1 point increase in adherence to this type of diet resulted in an 18 % reduction in the relative associated risk of a myocardial infarction [53]. It has also been found that the increased consumption of olive oil and whole grains, that are part of a Mediterranean diet, are both independently associated with a decrease in systolic and diastolic blood pressure [54]. Additionally, another major component of the Mediterranean diet, the increased intake of fish, has also been found to reduce both blood pressure and blood lipids [37, 55]. Finally, it been suggested that the Mediterranean diet may benefit insulin sensitivity and subsequently have a positive effect on decreasing cardiovascular disease [56]. This is further supported by reviews of Mediterranean food patterns and prevention of chronic disease, which have found that greater adherence to the Mediterranean style of diet was associated with a reduction in coronary heart disease [53, 57].

To date, very few studies have conducted randomised controlled based assessment of the effect of Mediterranean diet on health or cognitive outcomes. Recently a 3-arm control randomised study was undertaken using a Mediterranean diet pattern and nuts. The results of this study indicated that the Mediterranean diet has a protective effect on cardiovascular health and also cognitive function [58]. However, the mechanisms by which Mediterranean diet may actually achieve the observed improvements in cognitive performance or improved cardiovascular health have not yet been fully investigated. In particular the effect of this diet on the combination of arterial stiffness, central pulse pressures, circulatory biomarkers of inflammation and changes in BDNF. Additionally, while there have been numerous observational studies, to date no clinical trial of the effects of a Mediterranean diet, in elderly populations, using sensitive tests of specific cognitive functions, has been found.

## Cognition and combined exercise and diet

Exercise can potentially overcome the effects of a poor diet [59] and, in animal trials, exercise has been found to improve cognitive performance and increase hippocampal BDNF in rats with diet induced cognitive decline [60]. Conversely, it has been suggested that diet high in fruit and vegetables, combined with exercise, can assist the brain to cope with several types of insults and ultimately benefit brain function over time [59].

Healthy diet and exercise are associated with a reduced risk of cognitive decline and may provide opportunities to reduce the threat of cognitive decline more effectively than that which is currently understood [61]. With the increasing understanding of molecular biology it has been shown that diet and exercise can affect analogous molecular systems and that this can help lead us to understand a mechanism by which lifestyle, such as exercise and diet may positively influence brain plasticity [59]. Additionally, endothelial dysfunction has been associated with reduced cognitive performance [62], and, in a recent study of healthy older people, a combined Mediterranean diet and exercise intervention was found to provide enduring improvement in vascular endothelial function [63].

However, while there is support for the idea that Mediterranean diet and exercise will combine synergistically to reduce the rate of cognitive decline, there are two main aspects which require further investigation. Firstly, while there is an acknowledged need for a clinical trial of the effects of exercise and diet on cognitive function [61, 64], no such trial has been undertaken as yet. Secondly, the mechanisms by which Mediterranean diet and exercise may affect cognition have yet to be fully investigated. The current study aims to address both of these issues.

## Aims and study hypotheses

The primary aim of the current study is to examine the 6-month effects of increased exercise through walking, change to a Mediterranean diet, and a combination of both, on cognitive performance in an elderly population living independently in aged care facilities. It is hypothesised that measures of cognitive performance will be improved in both the exercise and dietary interventions, relative to the controls, and that the combined diet and exercise intervention will show the greatest improvement of all groups.

As a secondary aim, this study will also investigate the associations between cognitive function and blood based biomarkers and cardiovascular function, which have been proposed as mechanisms, or indicators of mechanisms, that may influence the rate of cognitive ageing. By investigating these variables, the current study aims to identify and target modifiable risk factors, as well as identifying objective biological indicators of the efficacy of interventions that are aimed at ameliorating the rate of cognitive ageing.

## Design and methodology

### Design

This is a randomised, controlled, four-arm parallel groups design. However, given the nature of the interventions, this study is not blinded as both investigators and participants will clearly know what the intervention is, as participants in the lifestyle arms will be actively working towards maintaining the lifestyle change. Participants will be randomly allocated to one of the following four groups:ControlExercise interventionDietary interventionCombined dietary and exercise intervention

The randomisation sequence will be created by permuting into blocks of 4. While allocation of participants to these groups will be randomised, for reasons of practicality, and to avoid cross contamination between the requirements of each group, when cohabiting couples participate, one person will be randomly allocated to a group and the other will be allocated to the same group.

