## Procedure

Eligible participants will be assessed over four sessions at their living facility. An overview of these sessions is provided in the trial flow diagram (Fig. 1). During the first session, which takes place in the participant’s home, participants are screened for eligibility and assessed with the MMSE and the GDS. Eligible participants are requested to visit their doctor to obtain consent to participate and then to have blood taken for biomarker analysis. Session 2, conducted in a central treatment room in that participant’s living facility, is undertaken once doctor’s consent and blood biomarkers have been obtained. During this visit baseline assessment of all measures are undertaken and participants are informed of the group they have been randomly allocated to. The third session, an in home visit at the 3 month time point, will collect participant recorded diet and/or exercise data where appropriate, and any adherence issues will be discussed. Mood, exercise and sleep questionnaires will also be undertaken at this session. As shown in Fig. 1, the final session will be a full assessment visit, assessing all measures. This will be conducted in a central treatment room of the facility at the 6 month time point. Participant recorded exercise and diet data will also be collected during this session, enabling the investigators to estimate adherence to the intervention.

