## Primary outcome

The primary area of interest in this study is the effect of the dietary and exercise interventions on performance in a battery of cognitive measures. The Swinburne University Computerised Cognitive Assessment Battery (SUCCAB) will be undertaken at baseline and at 6 months post baseline. The SUCCAB has been used to assess cognitive performance in previous studies [15, 66, 68]. Reliability and validity assessment has demonstrated that SUCCAB is sensitive to ageing and correlates strongly with memory subtests in the WAIS-IV [15]. The primary outcome will be memory response time calculated as a composite measure from the SUCCAB memory sub-tests.

Additionally, the MMSE will be used to screen for dementia as well as assessing any global effects of the interventions after 6 months.

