### Cognitive assessment

#### Swinburne University Computerised Cognitive Assessment Battery

The SUCCAB is a validated computer based cognitive battery consisting of eight measures that were developed, based on cognitive and neuroimaging literature, to focus on cognitive domains that were most likely to decline with increasing age [15]. This battery uses a simple 5 button interface and has been validated in other studies involving the elderly [70, 71]. The eight measures of cognitive functioning assessed by the SUCCAB consist of Simple and Choice Reaction Times, Immediate and Delayed Recognition, Congruent and Incongruent Stroop colour-words, Spatial Working Memory and Contextual Memory. Computerised measures provide consistency in measurement across participants, and a more automated approach in analysis. The primary outcome will be a composite measure comprised of spatial working memory, immediate, delayed and contextual recognition response time. Secondary outcomes will be response time and accuracy on the individual SUCCAB measures, with the exception of the Congruent Stroop and Reaction Time tasks, as ceiling effects for accuracy are anticipated, response times will be the sole outcome for these tasks.

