### Cardiovascular assessment

The effect of the intervention on cardiovascular factors will focus on peripheral and central blood pressures as well as arterial stiffness. These measures will be conducted using applanation tonometry with the SphygmoCor XCEL system. Aortic blood pressure and pulse pressure will be derived automatically, via a brachial blood pressure cuff. Standard brachial blood pressure will also be measured during this process, using an average taken over three recordings. Pulse wave velocity will be derived using a femoral cuff to capture the femoral waveform and tonometer pressure sensor to capture the carotid waveform.

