### Exercise assessment

#### The 6 min walk test

The 6 min Walk test will be utilised to indicate baseline fitness as well as improvement in fitness over the study [79]. In this assessment participants will between two markers placed 10 m apart. The objective of this test is to walk for as far as possible in 6 min.

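### Blinding is dropped for investigators as well as participants, for a reason that covers only participants and delivery, and arm-revealing records are collected in the 6-month test session

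*Protocol article*

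**What the plan says.** The Design section states that "this study is not blinded as both investigators and participants will clearly know what the intervention is". The supporting reason is that "participants in the lifestyle arms will be actively working towards maintaining the lifestyle change". No section of the article names a masked tester, scorer or analyst.

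Under Interventions, the diet arms record daily adherence and the exercise arms record their walking sessions. No such record is asked of controls. The Procedure section makes the last visit a full assessment of all measures at 6 months and adds: "Participant recorded exercise and diet data will also be collected during this session, enabling the investigators to estimate adherence to the intervention". The order of tasks within that visit is not given. Allocation is disclosed at the second session, where "baseline assessment of all measures are undertaken and participants are informed of the group they have been randomly allocated to".

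On the outcomes:
- The Primary outcome section says "The primary outcome will be memory response time calculated as a composite measure from the SUCCAB memory sub-tests". The section on the battery adds that "Computerised measures provide consistency in measurement across participants, and a more automated approach in analysis".
- The MMSE, besides screening, is repeated to look for global effects after 6 months.
- For the walk test, "The objective of this test is to walk for as far as possible in 6 min".
- Pulse wave velocity uses a femoral cuff and a "tonometer pressure sensor to capture the carotid waveform". Aortic and pulse pressures, by contrast, are derived automatically.

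Under Analysis, the covariates for the primary model are given only as those that may be relevant. They include baseline group differences in cognition or biomarkers, and cohabitation.

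**The concern.** A behavioural intervention has to be open to the people who carry it out and to those who deliver it. It does not follow that the person running the 6-month tests, or the person preparing and analysing the data, must know the arm. The article treats these as one question and gives up all masking on the strength of the first part.

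The 6-month visit then adds to the exposure. A participant who hands over a diet log, a walking log or both has shown the arm, and one with nothing to hand over is recognisably a control. If this happens before or during testing, it can affect how instructions are given, how much encouragement is offered and how borderline answers are scored.

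The likely direction matters too. The stated hypothesis is that both single interventions beat control and that the combined arm does best, and control is no change. Staff expectation would therefore tend to favour the hypothesis in every contrast with control, including the pooled ones planned as secondary analyses. Randomisation does not remove this bias, and nothing in the plan would separate it from a true effect.

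**Working it through.** **Step 1. Match the stated reason to each role.**

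| Role | Does the stated reason require it to be open? |
|---|---|
| Participant | Yes |
| Staff who deliver the intervention and discuss adherence | Yes |
| 6-month tester | No |
| Person preparing data and deriving the composite | No |
| Analyst | No |

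**Step 2. Rank the outcomes by exposure.**

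- More exposed: the 6-month MMSE (administered and scored by a person), the 6 min walk (effort-dependent, so encouragement could matter) and pulse wave velocity (a person captures the carotid waveform). None of these is the primary outcome.
- Less exposed: SUCCAB memory response time, the primary outcome, which a computer records. What remains is tester instruction or encouragement, any cleaning of response times, and a covariate choice left open to someone who may know the arms.
- Little exposed to the tester: automatically derived pressures, and bloods taken by a pathology company or the participant's practitioner.

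**Step 3. Reproduce the plan's own sample size.** Inputs from the Sample size section: four arms, f = 0.30, alpha 5%, power 80%. For a one-way ANOVA, the noncentrality is λ = N·f², with 3 and N − 4 degrees of freedom.

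- N = 128: λ = 128 × 0.09 = 11.52, power 0.810.
- N = 124: power 0.796.

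The smallest multiple of four that reaches 80% is therefore 128, as stated, which is 128/4 = 32 evaluable per arm. The recruited total follows as 128 × 1.15 = 147.2, rounded up to 148. Masking changes neither number.

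**Step 4. Size under an assumed bias.** The documents give no estimate, so a shift b of 0.1 to 0.2 SD is an assumption. Suppose there is no true effect and every lifestyle arm is shifted by b against control.

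*One arm against control*, two-sided t test, 32 per arm, 62 degrees of freedom, noncentrality b·√(32/2) = 4b:
- b = 0.1: noncentrality 0.4, rejection 6.8%
- b = 0.2: noncentrality 0.8, rejection 12.4%

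*Four-arm omnibus F*, N = 128. Three arms at b and one at 0 give f = b·√(3/16):
- b = 0.1: f = 0.0433, λ = 0.24, rejection 6.4%
- b = 0.2: f = 0.0866, λ = 0.96, rejection 11.1%

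For scale, 0.1 to 0.2 SD is 20 to 40% of the 0.5 SD average effect that the Sample size section takes from a meta-analysis of fitness training (0.1/0.5 and 0.2/0.5). These are simple tests of means. The planned analysis is a repeated-measures ANCOVA, so b should be read in units of the SD that the model actually uses.

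**The case against.** The strongest case against runs as follows.

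*The primary outcome is protected.* Response time is recorded by computer, and the article gives consistency and automation as reasons for using the battery. This stands. A reader might infer that primary scoring is open to the assessor's judgement, and the documents do not support that.

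*Staffing is unknown.* Testing takes place on location across at least 15 sites, and no section says how many staff there are or who runs which visit. This also stands. A reader might infer that existing staff could mask every step, but nothing in the article shows it. If one researcher runs all visits, a separate 6-month tester would mean extra staff. Nor does the article describe a step for accepting or rejecting tonometry traces, so no claim about bias there can rest on it.

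*The order within the session is not stated.* Testing may already come first, and someone other than the tester may collect the records. This is fair: exposure during testing is permitted by the text, not shown to occur.

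*Analyst masking is usually left to an analysis plan that is not shown.* This stands in part. A protocol that was silent would raise no point here. This one affirmatively declares the study unblinded, investigators included, and leaves the covariates open, so the declaration itself needs narrowing.

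*Participants stay open whatever is done.* This stands. Expectation and effort on timed and walking tests are untouched by any masking of staff, and could be the larger source of bias.

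**Conclusion.** The point holds as a limited, low-cost improvement. The article makes a design decision wider than its reason supports, and its 6-month visit permits the arm to be revealed while outcomes are being measured. The main exposure is in the tester-dependent measures outside the primary outcome. For the primary outcome the exposure is smaller and lies in instruction, data preparation and covariate choice.

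The figures in the working (about 7 to 12% for one arm against control, about 6 to 11% for the omnibus test) rest wholly on the assumed 0.1 to 0.2 SD. A reader might take them as evidence that such a bias exists. They show only what a bias of that size would do. The sample size is not affected. A reader might also infer that masking staff would make the comparisons free of expectation bias. It would not, because participants know their arm.

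**What to change.** 1. Reword the Design section so that the trial is open to participants and intervention staff, and state the masking status of the 6-month tester, the data preparation and the analysis separately.
2. In Session 4, complete all outcome tests (SUCCAB, MMSE, cardiovascular measures, walk test) before any record is collected or adherence discussed, and ask participants beforehand not to mention their arm.
3. Do SUCCAB cleaning, composite derivation, covariate choice and the primary analysis on coded arms, and unmask after the dataset is locked.
4. Where the team already allows it, have Session 4 run by someone not involved in that participant's allocation or 3-month visit. This is desirable but not required, since it depends on staffing that the article does not describe. Without it, the session order removes the prompt on the day but does not blind a tester who already knows the arm from an earlier visit.
5. State participants' own expectation as a remaining limitation.

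Items 1, 2, 3 and 5 cost a fixed session order, some coding work and a few sentences, with no new procedures. Item 4 may reduce scheduling flexibility across the sites. Some participants will disclose their arm regardless.
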